**Methods:**

We will train between 50–60 dialysis teams, led by social workers or nurses, to engage in ACP conversations with patients at their dialysis center regarding their preferences for end-of-life care. This implementation project uses the Knowledge to Action (KTA) Framework within the Consolidated Framework for Implementation Research (CFIR) to increase adoption and sustainability in the participating dialysis centers. This includes a curriculum about how to hold ACP conversation and coaching with monthly teleconferences through case discussion and mentoring. An application software will guide on the process and provide resources for holding ACP conversations. Our project will focus on implementation outcomes. Success will be determined by adoption and effective use of the ACP approach. Patient and provider outcomes will be measured by the number of ACP conversations held and documented; the quality and fidelity of ACP conversations to the HIGHway process as taught during education sessions; impact on knowledge and skills; content, relevance, and significance of ACP intervention for patients, and Supportive Kidney Care (SKC) App usage. Currently HIGHway is in the recruitment stage.

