## Methods/design

Our implementation of SDM-RSC is designed to demonstrate scalability within organizations that serve 80% of all dialysis patients in the US. The major goal of the HIGHway project is to routinize ACP and make it an expected part of regular workflow in the care of patients undergoing dialysis. In collaboration with a newly formed stakeholder advisory board comprised of kidney patients, and health care providers the intervention has been renamed HIGHway to convey the purpose of the project during this implementation phase. The new project name embodies its goal: the way to “Honor Individuals Goals and Hopes”. HIGHway trains and supports dialysis center social workers or nurses to communicate with their patients about their hopes and goals for their future care plans. This process, known as advance care planning (ACP), helps relieve patient concerns about the future, lays the foundation for better goal concordant care at the end of life, and fosters a deeper connection between the patient and the dialysis care team.

The project objectives are to:Implement the HIGHway intervention with a project team consisting of a social worker or nurse at 50 clinics, and train them to conduct ACP using best practices.Assist social workers/nurses to implement ACP into their regular workflow with personal coaching, webinars, and multimedia teaching materials.Use a dedicated web-based application software to guide social workers/nurses on the ACP process of patients in dialysis centers and provide resources for holding ACP conversations.Provide ongoing coaching through monthly teleconferences to bolster social worker/nurse skills through case discussion and mentoring.Evaluate the ACP training received by the nurses and social workers.Develop a long-term implementation and scale-up plan for training social workers/nurses in ACP in different dialysis centers in conjunction with the Coalition for Supportive Care of Kidney Patients, Forum of End of Stage Renal Disease (ESRD) Networks, the National Council of Nephrology Social Workers, the National Renal Administrators Association, and dialysis organizations.

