**Fig. 2 Fig2:**
[figure not shown]
Logic Model for HIGHway Project Implementation

HIGHway expands through both scale-up and scale-out on the previous SDM-RSC project intervention. Scaling up in numbers is achieved by enrolling a dialysis center team consisting of social worker or nurse, at 50–60 dialysis centers. Scaling-out happens by including a broader population of patients in the dialysis clinic instead of focusing solely on the seriously ill patients. The patient advisory council in the previous SDM-RSC study suggested of the inclusion of all patients within the dialysis center because they felt ACP would be of value to all dialysis center patients, they wanted ACP to be normalized as a regular part of care, and they wanted to avoid patients being alarmed by perceiving that they had been singled out for an “end of life” intervention.

Considering stakeholder advisory council recommendations and of the realities of implementation during the COVID pandemic, the social work training component of the SDM-RSC intervention has been streamlined and adapted to videoconference. Further, the computer application – a dedicated APP developed for this project – to guide documentation of the conversations has been made available on both Windows and IOS platforms. The overall aim is to increase the ability of the dialysis center teams to hold multi-disciplinary ACP conversations with all their in-center and home dialysis patients. A crucial component of this project is engagement of stakeholders throughout the process period. This will be accomplished through a national advisory council, chaired by the Coalition for Supportive Care of Kidney Patients. Key stakeholders, including patients, family members/caregivers, practitioners and organizational leaders will meet quarterly to inform the implementation process at each stage of the project.

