### Recruitment and consent process

Three large dialysis organizations have agreed to collaborate to implement this initiative. We will have a champion role that may be filled by any nephrologist at the site interested and willing to be part of the project. We are working in collaboration with the administration of the collaborating dialysis organizations to recruit social workers or nurses to participate. The dialysis organizations set their own criteria for which centers will be eligible to participate based on organizational priorities (e.g., dialysis centers who have completed installation of EMR, dialysis centers in a certain region). The dialysis organization will contact their employees with information about the HIGHway project using standard internal communication strategies such as email lists. Alternatively, others who learn of the project via marketing efforts by the Coalition for Supportive Care of Kidney patients may individually choose to apply directly to the project and will be enrolled if space is available in the training cohort. Currently, HIGHway is in the recruitment stage.

Standard consent processes as approved by the IRB will be used to enroll in the project training, and patients who are approached to participate in an audio recorded interview. As approved by the IRB, the consent for the audio-recorded conversation involves obtaining verbal consent, with a waiver of documentation of consent for patients who agree to have an ACP conversation recorded. To obtain this consent, a member of the project team will set up a WebEx call with social worker/nurse and patient and will explain the project, answer questions, and obtain verbal consent to audio record the conversation and create a transcription from the audio record. Once both have consented to the recording, the project team member will begin the recording, but leave the WebEx session so that the patient will have privacy during their conversation. Processes for temporarily storing the recording, creating, and storing a transcript for analysis, have been approved by the IRB.

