We plan to enroll 60 social workers or nurses total over the several training cohorts. The turnover and dropout are expected to be about 17%, resulting in target of 50 social workers/nurses who complete entire 9 months of training. The rational is the training capacity of the project. We expect that approximately 1,600 patients will receive ACP service because we will target each social worker/nurse conducting one ACP conversation per week during the 9 months of training, beginning after the first month. The proportion of patients who will participate in the post implementation survey is unknown. The target is 25% participation rate.

Quantitative analysis will be primarily descriptive, with descriptive statistics with confidence intervals to characterize survey responses on various questions. For several of the knowledge gain questions asked before and after the social workers engage in training, chi-square and t-tests will be used to assess change. Qualitative analysis will be used for both inductively and deductively assessing themes and subthemes. Given the short 2-year time frame for this project, and the proposed provision of ACP services to both seriously ill as well as stable dialysis patients, we have not tried to measure the impact of these activities on our end-users in terms of healthcare utilization or specific health outcomes or choices. Instead, the success of our ACP intervention—and receipt of goal-concordant care as the gold standard— is inferred from the high-quality communication based on our intervention, as demonstrated by the fidelity check of audiotaped ACP conversations and by patient survey responses. Further, we will measure the success of this implementation project by documenting that all ACP-related activities and discussions have taken place, by assessing the quality and completeness of GOC discussions, by mail-in survey of patients and family participating in discussions, and by qualitative interviews with selected patients.

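### The objective and adoption aim are set in centers, but enrolment, loss and completion are counted in workers, and workflow adoption is surveyed only at completion, so centers whose worker left drop out of that result

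*Protocol article*

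**What the plan says.** **Center-level statements.** The first project objective under Methods/design is to "Implement the HIGHway intervention with a project team consisting of a social worker or nurse at 50 clinics". The abstract (Methods) says "We will train between 50–60 dialysis teams, led by social workers or nurses" and names adoption and sustainability in the participating dialysis centers as the purpose of the implementation frameworks. The Implementation strategy section describes scale-up as "enrolling a dialysis center team consisting of social worker or nurse, at 50–60 dialysis centers".

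**Worker-level statements.** The Data collection section is the only place that sets enrolment, loss and a completion target. It reads "We plan to enroll 60 social workers or nurses total over the several training cohorts", then "The turnover and dropout are expected to be about 17" per cent, "resulting in target of 50 social workers/nurses who complete entire 9 months of training". The reason given for the number is training capacity.

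**Measurement.** The Data collection section assesses implementation outcomes by a survey of the participating social workers and nurses when they complete their nine months. Table 1 places adoption into workflow, barriers and future sustainability in the online worker survey. Conversation counts come from the app or, at sites not using it, from a weekly email report, which Table 1 says the social worker or nurse answers.

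**Entry.** The Recruitment and consent process section also lets people outside the organizations' own mailing "may individually choose to apply directly to the project and will be enrolled if space is available in the training cohort". No number of workers per center is fixed.

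**The concern.** The unit of the objective (center) and the unit of the retention plan (worker) differ, and the article gives no rule for converting one into the other. The larger problem is the timing of the adoption survey. A worker who leaves before month 9 does not reach it, so that worker's center may supply no information on whether advance care planning (ACP) became part of the workflow. The planned loss is about 10 of 60, so the missing group is not trivial. It is also selected: a center whose trained worker has left is where ACP is most at risk of having rested on one person.

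The single loss figure covers two different events. Leaving the post says little by itself about whether the center adopted ACP. Staying in post and stopping is non-adoption. For a project whose stated goal is to make ACP routine in dialysis care, the two carry different information.

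At stake is the denominator of the adoption result. Adoption among completers will tend to look better than adoption among the centers that entered.

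**Working it through.** **Inputs.** From Data collection: 60 workers enrolled, about 17% lost, 50 completing. From Methods/design: 50 clinics. From the abstract and Implementation strategy: 50–60 teams or centers. The number of workers per center is not stated, so the spread of workers over centers below is an assumption.

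**Step 1, the plan's own figure.** 60 × (1 − 0.17) = 49.8, about 50. Losing exactly 10 gives 10/60 = 16.7%. The worker arithmetic reproduces.

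**Step 2, one worker in each of 60 centers (natural reading).** Fifty completers are then 50 centers.
- Adoption among those surveyed, if all report it: 50/50 = 100%.
- Adoption among enrolled centers, if ACP stopped at the 10 centers whose worker left: 50/60 = 83%.
- If ACP continued at some of those 10 centers, the true figure lies between 83% and 100%. The survey as described cannot say where.

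**Step 3, fewer than 60 centers.** Let 60 workers come from C centers, with one or two per center. Then 60 − C centers have two workers and 2C − 60 have one. Ten workers are lost.
- Fewest centers with a completer, when every loss falls on a single-worker center: C − 10.
- Most centers with a completer, when second workers are lost first: C − (10 − (60 − C)) = 50.
- Under random loss, a single-worker center is lost with probability 10/60 = 0.1667, and a two-worker center with probability (10 × 9)/(60 × 59) = 0.0254.

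| Centers C | With one worker | With two | Range covered | Expected |
|---|---|---|---|---|
| 60 | 60 | 0 | 50 | 60 − 10 = 50 |
| 55 | 50 | 5 | 45–50 | 55 − 8.33 − 0.13 = 46.5 |
| 50 | 40 | 10 | 40–50 | 50 − 6.67 − 0.25 = 43.1 |

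The bottom of the last range is an extreme. All ten losses fall on the 40 single-worker centers with probability C(40,10)/C(60,10), about 1%.

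**Step 4, can other data fill the gap?** The weekly report is answered by the social worker or nurse, so it may end when that person leaves. A missing report could mean that ACP stopped or only that the reporter left. App data are collected by team, but the app is optional.

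**The case against.** The strongest reply has four parts.

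*The completer count is not a success criterion.* It is justified by training capacity, and the Implementation outcomes section defines success as adoption and effective use. This stands. A reader might infer that the project means to show implementation in 50 clinics by counting 50 completers; the article never says so.

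*The units nearly coincide.* The objective describes a team "with a project team consisting of a social worker or nurse at 50 clinics", and 60 enrolled with 50 completing matches 50–60 centers. This also stands: one worker per center is the natural reading, and the 40–50 range needs an assumed staffing pattern. It does not settle the matter, because Intervention activities allows social workers and/or nurses in a center, and because the survey gap in Step 2 arises even with exactly one worker per center.

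*Site-level data exist.* App counts by team and weekly site reports track activity, and fidelity audit and patient surveys add to it. This stands in part. They show what was done while someone reported, but the workflow and sustainability items sit in the end survey.

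*A condensed article need not give center identifiers or withdrawal forms.* Agreed, and their absence is not the point. The point is what the article does state: the survey's respondents and timing, and the unit of the completion target.

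Two stronger readings should be set aside. A worker who moves clinic and still counts as a completer, and a center counted as lost although a colleague carried on, are conceivable, but no section describes either. Nor does the article say that turnover and dropout will be reported merged; the 17% is a planning allowance.

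**Conclusion.** The point holds as a mismatch between a center-level aim and a worker-level measure taken only at completion. With one worker per center, the adoption figure could read 100% of those surveyed when it is as low as 83% of enrolled centers. This assumes that all 50 completers report adoption and that ACP stopped wherever a worker left. If 60 workers came from 50 centers, 50 completers would represent 40 to 50 centers, about 43 expected under random loss, so the worker target could be met with the clinic objective missed. That second result depends wholly on a staffing pattern the article does not give.

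The documents do not support saying that the figure of 50 is wrong or that it is put forward as evidence of implementation. The consequence is an adoption result that is hard to interpret, and it can be avoided cheaply.

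**What to change.** 1. State how many workers are enrolled per center, and align the Methods/design objective and the Data collection target on the unit, giving both numbers if they differ.
2. For every enrolled center, record at month 9, or when its worker leaves, whether ACP is still being done there. The collaborating dialysis organizations could be asked where the worker is no longer available.
3. Report adoption as active centers over all enrolled centers.
4. Show turnover (left the post) and dropout (in post, stopped ACP) separately.
5. Keep worker counts for the training and knowledge outcomes, where the worker is the right unit.

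The cost is one status item per center and a few aligned sentences. The adoption figure may come out less favourable than one based on completers alone.

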Social Worker/Nurse Online Survey	• Evaluation of training sessions includes both pre and post evaluation questions for comparison • Provide social worker survey (on-line) to evaluate participation in program, extent to which have adopted into ongoing workflow, identify facilitators and barriers, and assess future sustainability

Nephrologist and other clinic staff members will also have an opportunity to engage in both asynchronous and synchronous training. Training will focus on the HIGHWay model with opportunities to build skill around discussing ACP, and the role of the social worker, and importance of care coordination and interdisciplinary teamwork. Example video demonstrations and role plays will be used.

A computer application, The Supportive Kidney Care application (SKC App) enables dialysis center clinicians along the steps of an optimal ACP process. The first app was based on the Renal Physician Association “Shared Decision Making” Guidelines and provided tools to help dialysis center teams to assess prognosis and disease trajectory, guide discussion, and document goals of care with ACP forms. The revision of the app now follows the HIGHway roadmap and allows a more patient-centered, flexible process to occur and be documented. The app is optional for teams to adopt. We will evaluate the extent to which the app was useful and adopted by teams.

We work with the dialysis center teams to understand how ACP can be made a seamless part of regular workflow so that it does not require large amounts of additional resources. The process of folding ACP into existing workflow is part of the training and support provided to the dialysis center teams.

Around month 3–5 of the 9-month activity period, the social worker or nurse will select one patient to have an ACP conversation with and record the conversation with patient's consent. The lead social work faculty member will then hold an individual mentoring session with the social worker/nurse to provide supportive feedback to refine their communication skills.

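### Before/after knowledge answers from the same workers are to be tested with chi-square and t-tests without stating pairing; the ordinary chi-square test does not fit this design

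*Protocol article*

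**What the plan says.** The last paragraph of Data collection in the protocol article sets out the quantitative analysis. It opens with: "Quantitative analysis will be primarily descriptive, with descriptive statistics with confidence intervals to characterize survey responses on various questions". The next sentence covers several of the training items: "knowledge gain questions asked before and after the social workers engage in training, chi-square and t-tests will be used to assess change". No other hypothesis test is named in the article.

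Table 1 (Intervention activities), in the row for the social worker/nurse online survey, confirms the design: "Evaluation of training sessions includes both pre and post evaluation questions for comparison". No untrained or separate comparison group is described, so the before and after answers come from the trained workers themselves.

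The words paired, matched, linked and McNemar do not appear in connection with these tests. Neither do independent, two-sample or Pearson.

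The numbers of workers are in the same section: "We plan to enroll 60 social workers or nurses total over the several training cohorts", with dropout of about 17%, "resulting in target of 50 social workers/nurses who complete entire 9 months of training". The basis given for these numbers is training capacity. No alpha, power or effect size is stated for the knowledge questions.

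**The concern.** When one person answers the same item twice, the two answers are usually positively correlated. A chi-square test on a time-by-correct table counts each worker as two unrelated people. The information about change lies in who moved from wrong to right and who moved the other way, and that table discards it. A two-sample t-test does the same for scored items. In both cases the standard error of the change is wrong.

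With positive correlation the standard error is too large. P-values come out too high, intervals too wide, and a real gain from training may be reported as no clear change. Impact on provider knowledge and skills is a listed outcome (Implementation outcomes), and evaluating the training is a listed objective (Methods/design). The number of workers is fixed by training capacity, so precision lost in the analysis cannot be recovered by enrolling more.

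**Working it through.** **Number of pairs.** The article gives 60 enrolled and about 17% dropout: 60 × (1 − 0.17) = 49.8, or about 50, which agrees with the stated target. I use 50 pairs. This is an assumption for the knowledge items: the 50 are those who complete nine months, whereas initial training lasts six weeks (Implementation timeline), so the number of pre/post pairs may differ.

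**Other inputs, all assumed because the article gives none.** Two-sided alpha 0.05; a gain of 0.4 SD for scored items; 60% to 80% correct for binary items; within-person correlation 0 to 0.7 (scored) or phi 0 to 0.6 (binary).

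**Scored items, formula.** With equal SD s at both times, correlation r and n pairs:
- true SE of the mean change = s × √(2(1 − r)/n)
- SE used by an independent t-test = s × √(2/n)
- ratio = 1/√(1 − r), which is 1.41 at r = 0.5

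Large-sample check at r = 0.5: the unpaired test rejects only beyond 1.96 × 1.41 = 2.77 true standard errors, a two-sided probability of about 0.006. The expected paired statistic is 0.4 × √50/√(2 × 0.5) = 2.83, against 0.4 × √(50/2) = 2.00 for the unpaired one.

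**Scored items, simulation (20,000 data sets, n = 50 pairs).**

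| r | SE ratio | Type I error, unpaired | Type I error, paired | Power, unpaired | Power, paired |
|---|---|---|---|---|---|
| 0 | 1.00 | 0.050 | 0.049 | 0.51 | 0.50 |
| 0.3 | 1.20 | 0.021 | 0.048 | 0.51 | 0.65 |
| 0.5 | 1.41 | 0.007 | 0.050 | 0.51 | 0.79 |
| 0.7 | 1.83 | 0.001 | 0.053 | 0.52 | 0.95 |

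**Binary items, simulation (20,000 data sets, n = 50 pairs).** Type I error is at 60% correct both times; power is for 60% to 80%.

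| phi | Type I error, Pearson | Type I error, McNemar | Power, Pearson | Power, McNemar | Power, exact McNemar |
|---|---|---|---|---|---|
| 0 | 0.054 | 0.054 | 0.59 | 0.59 | 0.50 |
| 0.3 | 0.020 | 0.051 | 0.61 | 0.74 | 0.66 |
| 0.5 | 0.006 | 0.042 | 0.63 | 0.88 | 0.82 |
| 0.6 | 0.003 | 0.044 | 0.64 | 0.98 | 0.94 |

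**Constructed example.** Of 50 workers, 28 are right both times, 10 go from wrong to right, 2 from right to wrong, and 10 are wrong both times. That is 30/50 correct before and 38/50 after.
- Pearson: pooled proportion 68/100 = 0.68; 0.16² / (0.68 × 0.32 × 2/50) = 0.0256/0.008704 = 2.94, p = 0.086.
- McNemar: (10 − 2)²/12 = 5.33, p = 0.021.
- Exact McNemar: 2 × (1 + 12 + 66)/4096 = 158/4096, p = 0.039.

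The table was chosen to show that the choice of test can change the reading. It is not a forecast.

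**The case against.** The strongest reply is that the article leaves pairing unspecified and does not reject it. The t-test family includes the paired t-test, and McNemar's statistic is itself referred to a chi-square distribution. Assessing change on questions asked twice is compatible with a paired analysis. The article is also condensed, and the exact variant may be in the full protocol or the SAP, neither of which is shown. This largely stands for the t-test, which is ambiguous and not wrong. It stands less well for chi-square: in ordinary use that name means the test for independent observations, and the paired test has its own name. An analyst who ran both tests unpaired would still be following the sentence as written.

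A reader might also infer that the pre and post forms cannot be linked, or that workers with only a pre form will enter one side of the comparison. The documents support neither. The survey described as anonymous is the patient survey (Data collection), and Data Availability describes secure storage of identifiable data. Nothing is said about how incomplete pairs are handled. Linkage is therefore something to confirm, not a shown defect.

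Finally, all error rates and powers above rest on assumed inputs. At zero correlation the two approaches hardly differ, and the exact McNemar test is then the less powerful one.

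**Conclusion.** The point holds as a defect of specification. The article names tests for before/after answers from the same workers without stating pairing. Of the two, the ordinary chi-square test is wrong for the design and t-tests is ambiguous. The text does not show that the team will ignore pairing.

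If the tests were run unpaired with 50 pairs, two-sided alpha 0.05, a 0.4 SD gain and correlation 0.5, power would be about 0.51 instead of 0.79 and true alpha about 0.007 instead of 0.05. For binary items at phi 0.5, power would be 0.63 by Pearson against 0.88 by McNemar (0.82 exact). With positive correlation the error is conservative, so a fear of false claims of benefit is not supported.

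It would also go too far to say that the project's conclusions are at risk. The tests cover only several items in a mainly descriptive analysis. Success is judged on adoption and use of the approach, documented activity, the fidelity check, the patient survey and interviews. No sample size depends on these tests. Severity is minor to moderate.

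**What to change.** Replace the sentence on testing with wording to this effect: change will be assessed in workers with linked pre and post responses, using McNemar's test with the paired difference in proportions and its 95% CI for binary items, and the paired t-test or Wilcoxon signed-rank test with the mean paired change and its 95% CI for scored items. State in advance whether McNemar's test is asymptotic or exact, since the exact form is the more cautious at this size. If the full protocol or SAP already says this, align the article with it.

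Confirm that pre and post forms can be linked by worker, adding a worker code if they cannot, and report the number of workers with a pre form only. The article describes recruitment as still under way, with three cohorts planned, so any change to the forms could still reach workers not yet trained.

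The cost is one sentence of wording and, only if linkage is missing, a code on two forms. No extra data are needed.
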